# The youth concussion awareness network (You-CAN) - a school-based peer-led intervention to improve concussion reporting and social support: the protocol for a cluster randomized trial

**DOI:** 10.1186/s12889-020-8244-5

**Published:** 2020-02-05

**Keywords:** Concussion, School-based intervention, Peer education, Education, Adolescents, Brain injury

## Abstract

**Background:**

Concussion prevalence is increasing in the pediatric population, and is a matter of public health concern. Concussion symptoms can be physical, cognitive, emotional and behavioural, and last longer in high school aged youth than adults. Concussions are underreported in youth due to their lack of knowledge, social environment, perceived outcomes of reporting, norms, and self-efficacy. The Youth Concussion Awareness Network (You-CAN) is a school-based peer-led program designed to increase high school students’ intent to report a concussion, and provide social support to a peer. This study aims to investigate whether participation in You-CAN, a program grounded in service learning principles, impacts concussion knowledge, attitudes, intent to report a suspected concussion to an adult, and intent to provide social support to a peer. Secondary aims include assessing the implementation fidelity and acceptability of the intervention.

**Methods:**

This longitudinal study will use a cluster randomized trial design. Three high schools from six randomly selected Canadian school boards will participate and be randomized to three study arms: (1) You-CAN led by school staff; (2) You-CAN led by school staff and research team; and (3) untreated comparison group. Intervention arms 1 and 2 will deliver the You-CAN program and create a Concussion Council at their school. The Concussion Council will deliver a concussion awareness campaign and participate in an online showcase with other participating schools. In addition, arm 2 will have monthly video-calls with the research team. A survey based on the Theory of Planned Behaviour will be administered school-wide with all arms (1, 2, 3) at two time points (beginning {T_0_} and end {T_1_} of the school year). Exit interviews will be completed with the Concussion Councils and participating school staff.

**Discussion:**

This study will provide evidence of the effectiveness of a school-based peer-led concussion program on increasing concussion knowledge, attitudes, subjective norms, perceived behavioural control, intent to report a concussion to an adult, and intent to provide social support to a peer amongst Canadian high school students. It will also provide important information about the implementation and acceptability of the You-CAN program for high school students and staff.

**Trial registration:**

This trial is registered with the ISRCTN registry (ISRCTN64944275, 14/01/2020, retrospectively registered).

## Background

Concussion, also referred to as mild traumatic brain injury, is an injury to the brain that results from a direct blow to the head or body [1]. Concussion symptoms can be cognitive, physical, or emotional/behavioural, and can result in short and longer-term challenges [1]. Among children and youth in Canada, the prevalence of concussion has increased annually by 10.3% between 2005 and 2014 [2]. As prevalence continues to increase in the pediatric population [2, 3], concussion has been deemed a matter of public health concern [3, 4]. Concussion symptoms last longer in high school aged youth compared to younger children or adults [5]; however, high school aged youth have shown to lack basic knowledge about what a concussion is and the associated symptoms [6–8].

High school aged youth often do not report a concussion because they do not understand the severity of the injury [9], do not want to let their team down [9], or do not want to appear different from their peers [10]. Increased concussion knowledge has been shown to be associated with increased concussion reporting prevalence in high school aged youth [6, 11]. The Theory of Planned Behaviour (TPB) (Fig. 1) [12] has been used to conceptualize concussion-reporting behaviour and to evaluate concussion educational initiatives [13]. The TPB states that an individual’s attitudes, subjective norms and perceived behavioural control influence their intent to perform a desired health-related behaviour, which is closely linked with actual performance of the behaviour [12]. Peers within the high school setting play an essential role in influencing individuals’ attitudes and perceived subjective norms when performing health behaviours. Youth with a history of concussion report that their peers had negative attitudes towards their concussion and lacked knowledge about how to support them [10].

**Fig. 1 Fig1:**
[figure not shown]
The Theory of Planned Behaviour [12]

School culture of support has also been identified as a key factor in promoting students’ intent to report a concussion [14]. School-based environments can be an ideal environment for promoting positive health behaviours. Peer-led education programs in school settings continue to show great promise as a tool to promote positive behaviour change [15–17]. These programs involve having peers deliver instructional or behaviour change interventions within school-based environments [15–17]. Peer educators are a similar age to the target audience and can deliver educational messages in a more relatable way than adults [15]. In addition, peer-led education programs provide opportunities for students to engage in service learning. Service learning allows students to perform community service activities while gaining valuable knowledge and leadership skills [18].

The literature calls for the implementation of concussion education programs targeted at increasing awareness, promoting reporting and creating a safe environment [6]. Caron et al. [19] identified several concussion educational programs that have been developed for youth and target their concussion knowledge; however, these interventions have almost exclusively been targeted towards athletes [20–24] or are delivered by healthcare professionals [25]. To date, no school-based, peer-led interventions have been implemented and evaluated that aim to increase the concussion knowledge, attitudes and intended behaviours of high school students.

### Goals and research hypotheses

The goal of this study is to implement and evaluate the Youth Concussion Awareness Network (You-CAN), a school-based, peer-led service learning concussion intervention for Canadian high school students to advance concussion knowledge, awareness, and access to resources. The You-CAN intervention aims to increase high school students’ intent to report a concussion to an adult and intent to provide social support to a peer following a concussion.

The study has two main hypotheses: (1) You-CAN will result in improved concussion knowledge, attitudes, subjective norms, perceived behavioural control, intent to report a concussion to an adult, and intent to provide social support to a peer amongst Canadian high school students. (2) You-CAN will be an acceptable approach to advancing concussion knowledge sharing in Canadian high schools.

## Methods/design

### Study design

This longitudinal study uses a cluster randomized trial design with two intervention groups and an untreated comparison group (Fig. 2). This study has been approved by the Holland Bloorview Research Ethics Board (#18–826).

**Fig. 2 Fig2:**
[figure not shown]
Study enrollment, allocation and intervention flow

### Sample size

A sample size calculation was completed based on pilot administration of this study’s main outcome measure, the Concussion Reporting and Social Support Measure (CRSS-M) (see Outcome Measures section below). The sample size was calculated using an effect size of 0.20 (α = 0.05 and power = 0.80). This is in line with previously estimated effect sizes for school-based interventions conducted with high school aged youth [26–28]. As the CRSS-M is being administered in the school-setting with support from participating school boards, principals and school staff, we expect a low attrition rate (about 10%) from the beginning {T_0_} to end {T_1_} of the school year. Based on this information, we require 140 participants to complete the survey at each participating high school.

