#### Intervention assignment

Once consent to participate in the study is obtained from the school principals of the three size-matched schools, a member of the research team will randomly assign schools to one of three study arms: (1) You-CAN led by school staff (school-led You-CAN); (2) You-CAN led by school staff and research team (research-led You-CAN); (3) and comparison group (See Fig. 2). The random intervention assignment will be carried out using R software [29].

Both school-led You-CAN and research-led You-CAN will implement the You-CAN intervention, with the key difference being that schools in the research-led arm will participate in monthly video calls with the research team using the video communication platform Zoom [32]. These additional video call touchpoints will result in data collected for Hypothesis 2. The school-led You-CAN arm is the more feasible version of the intervention to be implemented in schools upon study completion. The comparison group will not implement the You-CAN intervention; however, the schools will participate in the school-wide administration of the CRSS-M (see Outcome Measures section below). The comparison group will be invited to deliver You-CAN in the subsequent year, after data collection has been completed. All schools regardless of study arm will receive an honorarium for participating and a summary of the study results.

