### Data analysis

#### Hypothesis 1

To examine the first research hypothesis, the following analyses will be performed. Data from the CRSS-M will be screened for outliers, and items will be screened for multicollinearity. CRSS-M data will be included for analysis if 90% of questions per section are answered and if there are matching unique identification codes from pretest {T_0_} to posttest {T_1_}. Descriptive statistics will be used to analyze demographics, true/false, checkbox and Likert scales responses. Paired sample t-tests will be used to detect changes in individual responses at pretest {T_0_} and posttest {T_1_} time points. A repeated measure ANOVA will be used to investigate differences in the 3 study arm schools (school-led You-CAN, research-led You-CAN and comparison group) from pretest {T_0_} and posttest {T_1_}. Co-variate adjustments will be completed depending on baseline means. Change scores from each You-CAN study arm will be compared across factors using a multifactorial ANOVA. Post-hoc tests (α = 0.05) will be used to determine the mean differences between each study arm. The school environment survey data will be analyzed through a descriptive univariate analysis. To determine the influence of school factors and additional activities completed by the Concussion Councils on CRSS-M change scores, co-variate adjustments and a multifactorial linear regression will be completed. Statistical analyses will be completed using SPSS [40]. Equivalent non-parametric approaches to analyses will be used should the data not meet necessary assumptions (e.g., normal distribution etc.).

#### Hypothesis 2

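### The stated 80% power for an effect of 0.20 with 140 students per school cannot be reproduced from its listed inputs, which include no ICC, and with 6 schools per arm it depends heavily on that ICC

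*Protocol article*

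**What the plan says.** The Study design section reads: "This longitudinal study uses a cluster randomized trial design with two intervention groups and an untreated comparison group". The Abstract (Methods) gives the number of clusters: "Three high schools from six randomly selected Canadian school boards will participate and be randomized to three study arms". Under Intervention assignment, "a member of the research team will randomly assign schools to one of three study arms", working within sets of three size-matched schools. That makes 18 schools, 6 per arm, with one school per arm in each board.

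The Sample size section bases its calculation on a pilot of the CRSS-M. "The sample size was calculated using an effect size of 0.20", with "α = 0.05 and power = 0.80". It expects roughly 10% loss between the two surveys and concludes from these items that "we require 140 participants to complete the survey at each participating high school". It does not say whether 0.20 is a standardised mean difference (d) or Cohen's f, or which arms are contrasted. It gives no ICC and no design effect.

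Data analysis, Hypothesis 1, plans paired t-tests and then: "A repeated measure ANOVA will be used to investigate differences in the 3 study arm schools". Change scores, covariate adjustment that depends on baseline means, and a regression on school factors follow. No term for the school as the randomised unit is named.

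**The concern.** In a trial that randomises schools, students in the same school tend to answer alike, and the number of schools limits precision. A per-school sample size with a stated power therefore needs an ICC. Here the article presents a per-school figure as the result of inputs that include none, so the reader cannot tell whether clustering was allowed for.

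The 80% figure is the standard against which a null result will be judged. If true power is nearer one half to two thirds, a null finding says much less than the stated power suggests. The article itself gives reason to expect schools to differ: it seeks varied cultures and both urban and rural areas, matches on school size because size is related to connectedness, and calls school culture a key factor in the intent to report.

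**Working it through.** **Inputs from the article.** Effect 0.20; alpha 0.05 (two-sided assumed); power 0.80; attrition about 10%; 140 students per school; 6 schools per arm. Completers per school: m = 140 × 0.9 = 126, or 756 per arm.

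**Inputs assumed.** 0.20 is read as d with SD 1, for a comparison of two arms. The ICC is shown over a range because the article gives none.

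**Step 1: reproduce 140 from the listed inputs.** n per arm = 2 × (1.96 + 0.8416)² / 0.20² = 2 × 7.849 / 0.04 = 392.4, so 393. After attrition, 393 / 0.9 = 437 per arm, and 437 / 6 = 73 per school. The stated 140 is 140 / 73 = 1.92 times this. One-sided, Bonferroni, paired and one-way ANOVA variants also fail to give 140 per school.

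One route does reach 140. A repeated measures ANOVA with f = 0.20, 3 groups, 2 times and zero pre-post correlation needs 124 students, or 126 in equal groups, and 126 / 0.9 = 140. That is a total for the whole trial, not a figure per school.

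**Step 2: the ICC that 140 would imply if it included an inflation.** Design effect (DE) = 756 / 392.4 = 1.93. Since DE = 1 + (m − 1) × ICC, ICC = 0.93 / 125 = 0.0074 (normal approximation).

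**Step 3: power for two arms of 6 schools, unadjusted.** SE = √[(ICC + (1 − ICC)/m) × 2/6]. Power comes from the normal distribution, or from the noncentral t with 6 + 6 − 2 = 10 df.

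| Assumed ICC | DE (m = 126) | SE | Power, normal | Power, t 10 df | d detectable with 80% power, t 10 df |
|---|---|---|---|---|---|
| 0.005 | 1.625 | 0.066 | 0.86 | 0.785 | 0.20 |
| 0.01 | 2.25 | 0.077 | 0.74 | 0.65 | 0.24 |
| 0.02 | 3.5 | 0.096 | 0.55 | 0.47 | 0.30 |
| 0.05 | 7.25 | 0.139 | 0.30 | 0.26 | 0.43 |

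**Step 4: the ICC at which power falls to 80%.** For m = 126: 0.0045 (t, 10 df), 0.0055 (t, 15 df, variance pooled over all 18 schools), 0.0074 (normal). For m = 140: 0.0053, 0.0063 and 0.0082.

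**Step 5: more students per school.** As m grows, SE² tends to ICC × 2/6. Even on the normal approximation, 80% power then needs ICC ≤ 6 × 0.04 / (2 × 7.849) = 0.015. At ICC 0.02 the ceiling is about 0.60 (t, 10 df).

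**Step 6: how the limit moves.**
- Both intervention arms pooled against comparison: 0.010 to 0.013.
- Baseline adjustment, with assumed student correlation 0.5 to 0.7 and school correlation 0 to 0.8: 0.0065 to 0.032.
- 0.20 read as f for the three-arm test: about 0.05 to 0.07.
- Bonferroni over 2 or 3 contrasts: 0.0004 to 0.0055.

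**Step 7: power with baseline adjustment.** Assume student correlation 0.5 and school correlation 0.8. The variance of a school mean becomes ICC × (1 − 0.64) + (1 − ICC) × (1 − 0.25)/126. At ICC 0.02 this is 0.0072 + 0.0058 = 0.0130, so SE = √(0.0130/3) = 0.066. Power (t, 10 df) is about 0.89 at ICC 0.01, 0.78 at 0.02 and 0.53 at 0.05.

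**The case against.** A reader might infer that clustering was ignored. The article does not show that. It states no design effect, but 140 is nearly twice the unclustered need, so an unreported inflation cannot be excluded. The pilot is not shown, and a journal article condenses a fuller protocol that may hold the detail.

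A reader might also take 0.005 as the ICC beyond which the design fails. That too goes further than the article allows. The limit belongs to one scenario: d = 0.20, two arms, no baseline adjustment and t-based degrees of freedom. The planned analysis uses both surveys and allows covariates. Matching within boards would take board and size differences out of the error if the analysis respects it. If 140 already means completers, power at ICC 0.005 is 0.81.

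All of this stands and rules out a single threshold. It does not make the listed inputs yield 140 per school. The article claims that they do, so the point is more than a detail left to another document. That the answer depends so strongly on metric and contrast is part of the problem, because the paragraph fixes neither.

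**Conclusion.** The sample-size paragraph is wrong as written and must be corrected. Its inputs do not reproduce its output (about 73 against 140 per school for d = 0.20 without clustering), and its unqualified 80% power has no stated ICC behind it.

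For an unadjusted comparison of two arms at d = 0.20, 80% power holds only up to an ICC of about 0.005 to 0.008, over 126 to 140 completers and t or normal theory. At assumed ICCs of 0.01 and 0.02 with 126 completers, power is about 0.65 to 0.74 and 0.47 to 0.55. These figures rest on 0.20 being d, a two-sided 0.05 test, equal school sizes, no board blocking and assumed ICCs.

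It does not follow that the trial is underpowered for the analysis finally used. The documents give neither the ICC nor the correlations needed to decide that.

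**What to change.** Rewrite the Sample size paragraph to state:

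- whether 0.20 is d or f, and which contrast it refers to;
- 6 schools per arm, and whether 140 is the number surveyed or the number with usable data at both times;
- an ICC range estimated from the pilot or from the T0 survey;
- power, or the difference detectable with 80% power, across that range, on school-level degrees of freedom.

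Replace the unqualified power of 0.80 with that figure. Tie it to a named analysis that adjusts for baseline, blocks on board and accounts for school, through a random effect or a school-level analysis. If several arm contrasts are each to support a claim, base the power on the alpha actually used for each.

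The text should not say that adjustment restores 80% power. Under the assumed correlations in Step 7 it does so at ICC 0.01, but not at 0.02 or 0.05.

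The cost is text and a short calculation. The downside is that the stated power becomes less favourable.

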### Participants and procedure

#### School board recruitment

Six public school boards in six Canadian provinces and/or territories will be randomly selected to participate in the study. This allows for the intervention to be evaluated with exposure to different cultures across Canada as well as both urban and rural areas. Within each province, school boards will be eligible for inclusion in the random selection process if they are primarily English-speaking and contain at least six co-ed high schools. School boards will be excluded from the random selection process if they outline an active consent process (i.e. guardian required to provide consent for student to participate) on their website. Randomly selected school boards will be invited to participate, and research applications will be submitted at the school board level. If a randomly selected school board declines participation then an additional school board will be randomly selected. This process will continue until six school boards have expressed interest and granted approval for schools within their school board to participate in the study.

#### School recruitment

After obtaining approval at the school board level, three schools within each board will be invited to participate. Schools will be included in the randomization process if they are: (1) primarily English-speaking, (2) co-ed, and (3) enrol students in grades 9–12. They will be excluded if they: (1) have less than 100 students, (2) only teach distance education, or (3) are an alternative school setting. The randomization assignment will be completed using R software [29]. All school principals from the randomly selected schools will be contacted through email and telephone via publicly available contact information in order to confirm participation and provide consent on behalf of the school. Schools will be further excluded if (1) they already have an established concussion club or (2) no other size-matched schools chose to participate.

Selected schools will be matched for school size prior to the random allocation to the study arms. School size is shown to be associated with school connectedness, students’ beliefs that teachers within the school care about them as individuals, and care about their learning [30, 31]. The following categories will be used to capture school size: (1) large population size (1000+ students), (2) medium population size (400–1000 students), and (3) low population size (less than 400 students). If three schools of matched size are not interested in participating, a different size category will be selected and invited to participate. If no size-matched schools agree to participate, then the school board will be excluded from the study and a new school board will be randomly selected to participate.

#### Intervention assignment

Once consent to participate in the study is obtained from the school principals of the three size-matched schools, a member of the research team will randomly assign schools to one of three study arms: (1) You-CAN led by school staff (school-led You-CAN); (2) You-CAN led by school staff and research team (research-led You-CAN); (3) and comparison group (See Fig. 2). The random intervention assignment will be carried out using R software [29].

Both school-led You-CAN and research-led You-CAN will implement the You-CAN intervention, with the key difference being that schools in the research-led arm will participate in monthly video calls with the research team using the video communication platform Zoom [32]. These additional video call touchpoints will result in data collected for Hypothesis 2. The school-led You-CAN arm is the more feasible version of the intervention to be implemented in schools upon study completion. The comparison group will not implement the You-CAN intervention; however, the schools will participate in the school-wide administration of the CRSS-M (see Outcome Measures section below). The comparison group will be invited to deliver You-CAN in the subsequent year, after data collection has been completed. All schools regardless of study arm will receive an honorarium for participating and a summary of the study results.

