#### Student and school staff participants

Schools assigned to the school-led You-CAN and research-led You-CAN arms will deliver the intervention. Within these schools, one or two school staff members will be recruited to participate in this study. School staff will be made aware of the study through direct communication with their school’s principal. In addition, two or more students will be recruited to participate in their school’s Concussion Council, and will be made aware of the study through their school principal and participating school staff member(s). All students at the participating schools will be made aware of, and invited to participate in, the school-wide administration of the CRSS-M.

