### Outcome measures

The instruments and data collection tools selected, as well as the timeline for implementation are found in Table 2. All data will be de-identified and stored on a secure network. Only the research team will have access to the final dataset.

**Table 2 Tab2:** You-CAN intervention and data collection timeline

	2019				2020				
	Sept	Oct	Nov	Dec	Jan	Feb	Mar	Apr	May
Informed consent: principals, school staff, council members	X								
Intervention time points									
Concussion awareness campaign						X	X		
*Rowan Stringer Concussion Awareness Campaign Showcase*								X	
Monthly video call with research team^*a*^		X	X	X	X	X	X	X	X
Outcome Measures									
School environment survey		X							
Concussion Reporting and Social Support Measure (CRSS-M) (T_0_)		X							
Web portal analytics		X	X	X	X	X	X	X	X
Field notes from monthly video calls^*a*^		X	X	X	X	X	X	X	X
Campaign details survey					X				
Content created					X	X	X	X	
Additional activities tracking sheet								X	
Post-showcase evaluation survey								X	
Exit interviews									X
Concussion Reporting and Social Support Measure (CRSS-M) (T_1_)									X

^*a*^*Only applies to the You-CAN led by school staff and research team arm*

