#### Concussion reporting and social support measure (CRSS-M)

The CRSS-M is an outcome measure developed and piloted by the research team that will be delivered to students at the beginning {T_0_} and end {T_1_} of the school year, pre- and post-participation in You-CAN. The CRSS-M was informed by the Theory of Planned Behaviour [12] and includes questions regarding demographic information (i.e. concussion history, sport participation, etc.), concussion knowledge, attitudes, perceived behavioural control, subjective norms, intent to report concussion symptoms to an adult and intent to provide social support to a peer. The CRSS-M also contains a 6 question unique identification code that allows individual surveys to be anonymously linked. It contains 57 questions including yes/no, multiple choice, checkbox, open-ended, true/false and Likert scale questions and will take approximately 10 min to complete. The CRSS-M was developed in order to provide questions about concussion that are relevant for a wide variety of high school students (sport and non-sport related questions).

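### Students consent and complete the T0 survey after You-CAN schools know their arm, so survey uptake, and to a lesser degree T0 responses, can differ by arm

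*Protocol article*

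**What the plan says.** All references are to the protocol article.

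- **Intervention assignment.** The allocation step is worded "a member of the research team will randomly assign schools to one of three study arms", using R. Its timing is tied to the principals' agreement: "Once consent to participate in the study is obtained from the school principals of the three size-matched schools". Nothing says that the result is withheld from the schools for any period.
- **Student and school staff participants.** Further recruitment depends on the arm. Of the schools assigned to You-CAN it says: "Within these schools, one or two school staff members will be recruited to participate in this study", and "two or more students will be recruited to participate in their school’s Concussion Council". Comparison schools have neither. Every student in every arm is invited to the survey.
- **Informed consent.** Each student gives his or her own active consent to the survey.
- **Table 2 (Outcome measures).** The row "Informed consent: principals, school staff, council members" is marked in September 2019. The T0 CRSS-M is marked in October 2019. The row "Monthly video call with research team", for the research-led arm only, is marked from October to May. Campaigns are in February and March.
- **Concussion reporting and social support measure (CRSS-M).** The two administrations are described as "pre- and post-participation in You-CAN".
- **Data analysis, Hypothesis 1.** Surveys enter the analysis only if linked at T0 and T1. The methods include paired tests, repeated-measures ANOVA and comparison of change scores. Covariate adjustment is conditional on what the baseline means show.

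**The concern.** Randomising schools makes the schools comparable. It makes the students comparable only if the way they enter the sample cannot depend on the arm. Here students enter by volunteering for a survey in schools that, at least in the two You-CAN arms, already know their allocation. They do so after arm-specific recruitment of staff and council members has been scheduled.

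Two things are at stake. First, uptake may differ, so that the students analysed in one arm are more interested in the topic than those in another. Second, some T0 answers may be given by students who know that their school is a You-CAN school, or who are on its council, so the baseline may not be wholly free of the allocation.

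**Working it through.** **1. Order of events.** No randomisation date is printed, but it can be bounded.

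| Step | Source | Timing |
|---|---|---|
| Principals consent | Intervention assignment; Table 2 | September |
| Schools assigned | Intervention assignment | After principals' consent |
| Staff and council consent, You-CAN schools only | Student and school staff participants; Table 2 | September, after assignment |
| Student consent and T0 CRSS-M, all arms | Informed consent; Table 2 | October |
| Research-team calls, research-led arm | Table 2 | From October |
| Campaigns | Table 2 | February and March |

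Staff and council members are sought only where a school has been assigned to You-CAN, and their consent is a September entry. On the printed timetable, allocation is therefore known in those schools by September and T0 follows.

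**2. What uptake decides.** A student who skips T0 cannot be linked and is never analysed. There is room for selection: Sample size asks for 140 students per school, and in a school of 1,000 or more that is at most 140/1000 = 14% of enrolment.

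**3. Size.** The plan gives no figure on this point to reproduce. It gives no uptake rate, no pre-post correlation and no estimate of early exposure. The values of *p*, *g*, *r* and *e* below are assumptions shown as ranges. Only the design effect of 0.20 comes from the article.

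*(a) Stable selection.* Let *p* be the difference between arms in the share of keen students, and *g* their advantage in score at both time points. The entry difference is D = p × g. With p = 0.05 to 0.20 and g = 0.3 to 0.5 SD:
- D = 0.05 × 0.3 = 0.015 SD to 0.20 × 0.5 = 0.10 SD.
- Bias in a change score: D − D = 0.
- Bias after adjustment for T0 with slope *r* (equal variances, so *r* is the pre-post correlation): D × (1 − r). With r = 0.5 to 0.7 this runs from 0.015 × 0.3 = 0.0045 SD to 0.10 × 0.5 = 0.05 SD.

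*(b) Selection related to change.* If keen students change by *h* SD more than others between T0 and T1, the bias in the change score is p × h and does not cancel. For each 0.1 SD of *h*, it is 0.05 × 0.1 = 0.005 to 0.20 × 0.1 = 0.02 SD. The article offers no basis for a value of *h*.

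*(c) Early exposure.* If T0 in You-CAN schools is already raised by *e*, a true effect of 0.20 appears in change scores as 0.20 − e.
- For e = 0.02, 0.05 and 0.10 this gives 0.18, 0.15 and 0.10.
- With T0 adjustment it is 0.20 − r × e. At e = 0.10 and r = 0.5 to 0.7 this is 0.15 to 0.13.
- The upper values are a bracket, not an expectation, because the campaign comes months after T0.

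Routes (a) and (b) can act in either direction. Route (c) shrinks the effect.

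**The case against.** The case on the other side is substantial, and much of it stands.

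- **All arms are approached alike.** Every student is invited, the same information letter and consent procedure apply, and every school receives an honorarium. Sample size describes support from boards, principals and staff without limiting it to You-CAN arms. This stands: selection could act only through different uptake, not through who is asked. A reader might infer that councils or their staff promote the survey; nothing in the article says so.
- **The analysis absorbs a level difference.** A reader might convert an uptake gap into a difference at entry and set it against the 0.20 target. For example, 60% against 40% uptake and a correlation of 0.3 between willingness and intent give 0.3 × (0.966 − 0.644) = 0.097 SD. The documents do not support that comparison. All three inputs are assumed, the planned change-score and repeated-measures analyses largely cancel a stable difference, and in that example the more selected comparison sample scores higher, so the raw bias runs against You-CAN.
- **T0 precedes the campaign.** This stands. Table 2 works in whole months, so sharing October with T0 does not show that calls came first. A reader might also take the web-portal row as student use in October. It is a download of analytics for a portal with one login per school, and does not show that the surveyed students were exposed.
- **T0 was probably complete when the article appeared.** T0 was scheduled for October 2019 and publication was in February 2020. This limits the remedy, not the finding.
- **Figures 2 and 3 are not available here** and may clarify the timing. The order in the text and in Table 2 is nevertheless explicit.

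These points do not remove the core: the arm is known in You-CAN schools before students decide whether to enter, and no concealment until T0 is described.

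**Conclusion.** The point holds as a limitation of design. On the article's own sequence, student entry and the baseline follow allocation, and entry at T0 is a condition for being analysed. Survey uptake can therefore differ by arm, and T0 responses can too, to a lesser degree. Adjusting only if baseline means look different does not deal with selection on motivation that is not measured.

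The size is unknown. Under the assumptions shown, stable selection leaves nothing in change scores and at most about 0.05 SD after T0 adjustment. The routes that matter are selection related to differential change, for which the article gives no basis for a figure, and early exposure at T0, which is probably small. The documents do not show that differential uptake occurred, that T0 was contaminated, or that the allocation of schools was compromised: principals consent before assignment. The conclusion rests on reading Table 2 together with the recruitment text, since no date of randomisation or disclosure is printed.

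**What to change.** **Any school or cohort not yet surveyed.** Complete student consent and the T0 CRSS-M in all three schools of a board before the arm is disclosed to principals, staff or students. The allocation can be generated as planned and released once T0 closes. Start council recruitment and the research-team calls afterwards, and state this order in the text and in Table 2. The cost is that councils start a few weeks later, with campaigns still in February and March.

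**Schools where T0 is already done.**
- Report T0 participation by arm, as students consenting over students enrolled. The school environment survey already asks principals in all arms for the school population.
- Add a sensitivity analysis adjusted for T0 score and for student characteristics on the CRSS-M, such as concussion history and sport participation, whatever the observed baseline means show. Present it beside the change-score result, because the two respond differently to selection and to early exposure.
- State as a limitation that neither step removes selection on unmeasured motivation, and that adjusting for a T0 already affected by allocation can itself bias the estimate.

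This needs no new data collection, only a specification fixed before the arms are compared.
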